### Randomization, allocation concealment, and blinding

After enrolment, participants will be randomly assigned to the active or placebo group in a 2:1 manner. The randomization will be prepared by the trial statistician and will be implemented within the REDCap (Research Electronic Data Capture) database system by the data manager. The randomization will include a technical stratification regarding singleton/twin status. Singletons will be assigned to the treatment groups by simple randomization in a 2:1 manner (active: placebo). Twins will also be randomly assigned to the treatment groups in a 2:1 manner (active: placebo); however, twins will be randomized together, i.e., each pair will be randomized into the same treatment group. Thus, the ratio of 2:1 will be implemented on the pair-level. In addition, the randomization of twins will be blocked (block length: 3 pairs (i.e., 6 subjects)) due to the low number of twins expected in this study. The rationale for randomizing twins into the same treatment group is the difficulty for parents to ensure the strict separation of the daily (blinded) feeding products to their infants over the course of 6–8 months. Study investigators, all involved study staff, and the parents of the participants are blinded to treatment. Allocation of subjects will be performed concealed (i.e., without knowledge of group allocation) by authorized site personnel using REDCap where each participant will be allocated to one out of fifteen kit codes for the interventional product (10 codes active, 5 codes placebo). The product will be labeled with the kit codes by staff, which is unblinded, but not otherwise involved in the study.

In general, unblinding per subject will be performed at the individual end of the study (if the patients are sensitized to HE, CM, PN, or HN at V5, they are instructed to continue consuming the study product until V6 takes place.) In case of serious allergic reactions suspected to be related to the study intervention, unblinding should be performed on the decision of the investigator. In order to ensure the unblinding process, emergency envelopes, providing information on the individual interventional group the subject is assigned to, are stored at the study center. Once unblinding has been performed, it will be documented in the source data, reported to the principal investigator and will result in the subjects’ early discontinuation of intervention.

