### Study procedures

Screening (visit 1, V1) of the subjects will take place at 4–8 months of age in infants who developed eczema. Written informed consent will be obtained from the parents by the study physician. During V1, the inclusion and exclusion criteria will be checked. Subjects who are eligible for participation in the study will be randomized to one of the two study groups. Information on demographics, subject/family characteristics, relevant medical history, medication, and nutrition will be recorded. In addition, anthropometric measurements and physical examination will be performed, including the assessment of eczema severity using SCORAD [20] and EASI score [21]. Blood from the participant and its mother will be drawn. Skin swabs and saliva samples will be collected for the mechanistic subprojects by the study staff. Skin swabs are collected and preserved in DNA/RNA shield collection tubes containing medium (DNA/RNA Shield; Zymo Research, Irvine, CA, USA). Saliva samples are collected both with Zymo Swabs as well as with Salimetric Swabs (SalivaBio Swab; Suffolk, Great Britain). Transepidermal water (TEWL) measurement will be performed with the Tewameter TM Hex (Courage + Khazaka electronic GmbH, Germany). Palmar linearity pattern will be analyzed and documented by palm photographs.

The investigator will instruct the parents to collect stool samples (using OMNIgene-GUT tubes, OMR-200; DNA Genotek, Ontario, Canada) from the infants at home for the mechanistic subprojects. The parents should further collect a dust sample (using dustream® collector DU-ST-1; Indoor Biotechnologies LTD, Cardiff, UK) from the infant´s bed (or the parent´s bed, if the child sleeps in this bed four nights or more per week) and the living room.

The first feeding of the study product will be performed at the study site. Parents will be asked to maintain an e-diary from V1 to V5/V6. The e-diary contains questions concerning the patient´s diet, compliance, and tolerability of the study product, eczema severity (POEM score [22]) and concomitant medication.

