### Sample size calculation

Analyzing 120 infants (80 in the active group and 40 in the placebo group) will result in at least 80% power to detect a difference in the primary endpoint (food allergy after 6–8 months of intervention) of 10% in the intervention group vs. 33% in the control group, based on a two-sided chi-squared test with significance level 5%. In order to compensate for a potential dropout-rate of about 20%, 150 infants will be randomized (100 infants to the active group and 50 infants to the placebo group). As the number of twins included to this study is expected to be very low (i.e., one or two pairs), the correlation due to twin status is not taken into account for the sample size calculation.

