### Statistical analysis

The primary analysis of the primary endpoint will be performed by logistic regression with (fixed) factor treatment group (active, placebo) taking the correlation of twins into account. From this model, the odds ratio for treatment will be calculated with 95% confidence interval and a *p*-value for the treatment group comparison. The analysis will be performed on the full analysis set (FAS) without imputation of missing values. The significance level will be set to 0.05 (two-sided). All other analysis will be considered explorative. Several explorative sensitivity analysis will be performed for the primary endpoint: a re-run of the primary analysis model without taking the correlation of twins into account and a re-run of the primary analysis model with the per- protocol population (instead of the FAS). In case of relevant differences between the treatment groups with respect to baseline variables, the primary analysis will be repeated with further adjustment variables (FAS population). Moreover, several subgroup analysis will be conducted regarding the following subgroups: carrier of mutations in the Filaggrin gene; infants with at least one parent with eczema; infants with at least one parent with atopic diseases (asthma, rhinoconjunctivitis, eczema); breastfed children/formula fed children, children with impaired skin barrier function (measured with TEWL); and household allergen exposure. Subgroup analysis will be performed by additionally including the subgroup variable and the interaction term (subgroup*treatment group) into the primary analysis model (FAS population). In case subpopulations regarding to the consumption of CM exist, these subpopulations will be analyzed separately (FAS population).

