## Discussion

This clinical trial, including 150 infants with eczema at 4–8 months of age, will investigate whether an early introduction of baked HE, CM, PN, and HN can reduce the risk for developing food allergy in the first year of life.

The study population of this trial consists of infants with eczema, who are at risk for development of further atopic conditions, and therefore does not represent the general population. Interestingly, it has been reported that even in children with food allergy but without eczema, an impaired skin barrier function occurs [24]. One third of the infants taking part in our HEAP study, who were sensitized against HE, had no atopic dermatitis at the screening visit [10]. Nevertheless, Natsume et al. were able to show that the introduction of small amounts of heated HE is particularly effective in infants with atopic dermatitis that might already be sensitized [13]. It needs to be shown, whether this finding can be confirmed and whether this approach is suitable for other food allergens. Besides the introduction of HE, Natsume et al. treated participants’ eczema attentively throughout the whole study period. In our trial, the treatment of the subjects’ eczema will not be part of the study intervention. However, during the interventional period of our study treatment of eczema will be assessed and the impact of an early introduction of small amounts of allergenic foods in regard to severity of eczema will be evaluated. Severity grading will be performed by using different objective and standardized diagnostic systems (POEM, SCORAD, and EASI diagnostic score).

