Within this study, one of our aims is to assess the safety of an early introduction of small amounts of allergenic foods in infants with eczema in the first year of life regarding the occurrence of immediate type allergic reactions, gastrointestinal symptoms, and growth. Currently, children with moderate to severe eczema are routinely screened for sensitization against the most important food allergens [27]. In order to avoid anaphylactic reactions occurring at home within the first feeding, screening for sensitization against certain food allergens needs to be conducted before these foods are introduced into the infant´s diet [27]. The results of this trial will help to clarify, if an early introduction of potentially allergenic foods in high-risk infants can be done safely by starting from a very small dose and increasing the amount in a stepwise manner, even without screening for sensitization before.

The results of the trial will be submitted for publication in peer-reviewed journals and will further be communicated to participants, health care providers, and professional groups including health visitors and midwives, as they may affect current dietary recommendations regarding the prevention of food allergy.

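### The primary model carries no baseline covariate, and adjustment waits for an observed imbalance; one prespecified prognostic covariate would gain precision, though the primary test and its stated power stand

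*Protocol article*

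**What the plan says.** Under Statistical analysis, the primary endpoint is analysed by logistic regression on the full analysis set. Treatment group is the only fixed factor, and twin correlation is allowed for. Every other analysis is declared explorative, including this one: "In case of relevant differences between the treatment groups with respect to baseline variables, the primary analysis will be repeated with further adjustment variables".

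The subgroup list in the same section covers filaggrin mutation, parental eczema, parental atopy, breast or formula feeding, skin barrier function and household allergen exposure. Subpopulations by cow's milk consumption are analysed separately. Sensitisation at entry is not listed.

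Under Randomization, the only stratification is singleton versus twin: "Singletons will be assigned to the treatment groups by simple randomization".

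Under Study procedures, SCORAD and EASI are assessed at V1, and "Blood from the participant and its mother will be drawn". The text states no specific IgE assay at V1 and describes the skin prick test at V5. The visit table is not reproduced in the text at hand.

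The Discussion says of the earlier heated-egg trial that the approach "is particularly effective in infants with atopic dermatitis that might already be sensitized", and that this needs confirmation. It also says the results will help to show whether stepwise introduction is safe "even without screening for sensitization before".

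**The concern.** Covariates earn their place in a randomised comparison by predicting the outcome, and they should be chosen before the data are seen. An imbalance trigger reverses both: a strong predictor that happens to be balanced is left out, a weak one that happens to be unbalanced is brought in, and the adjusted result exists only if someone judges a difference to be relevant. What counts as relevant, and which variables qualify, may be set out in the full protocol or the statistical analysis plan, so that is not the complaint. The trigger itself is stated in the article.

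Sensitisation at entry is the obvious candidate. The Background says that about half of infants with eczema become sensitised and about one third become allergic, and that two thirds of infants in the heated-egg trial were sensitised at enrolment. Levels 1 and 2 of the primary endpoint both require sensitisation. The plan is also uneven: continuous secondary endpoints are adjusted for baseline where available, while the binary primary endpoint is not adjusted for anything.

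At stake are the precision of the primary estimate, the value of the adjusted result as supporting evidence, and a planned description of the infants whom the Discussion singles out.

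**Working it through.** **Inputs from the article.** Two-sided 5% level; 80 active and 40 placebo infants analysed; "10% in the intervention group vs. 33% in the control group"; 20% dropout and 150 randomised.

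**Assumptions, not in the article.** Share sensitised at V1: 30%, 50% or 67%. Odds ratio of V1 sensitisation for food allergy: 1, 5, 10 or 20.

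**1. The plan's own figure.** Expected events are 80 × 0.10 + 40 × 0.33 = 21.2, so the pooled risk is 21.2/120 = 0.1767.

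- SE under the null = √(0.1767 × 0.8233 × (1/80 + 1/40)) = 0.0739
- SE under the alternative = √(0.10 × 0.90/80 + 0.33 × 0.67/40) = 0.0816
- Power = Φ((0.23 − 1.96 × 0.0739)/0.0816) = Φ(1.045) = 85.2%

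Exact enumeration of the chi-squared test gives 86.2% without and 81.1% with continuity correction. The dropout step is 120/(1 − 0.20) = 150. The claim that the design "will result in at least 80% power to detect a difference in the primary endpoint" therefore holds.

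**2. Chance imbalance.** For a factor with share q, the SD of the between-group difference is √(q(1 − q)(1/n₁ + 1/n₂)). With q = 0.5 and 80 vs 40 it is √(0.25 × 0.0375) = 0.0968, so P(difference ≥ 10 points) = 2 × (1 − Φ(1.03)) = 30%, and P(≥ 15 points) = 12%.

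| Groups | ≥ 10 points (q = 30% to 67%) | ≥ 15 points |
|---|---|---|
| 80 vs 40 | 26–30% | 9–12% |
| 100 vs 50 | 21–25% | 6–8% |

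At q = 0.5 and 33% overall placebo risk, the risks in non-sensitised and sensitised infants are 16.4% and 49.6% (odds ratio 5) or 6.8% and 59.2% (odds ratio 20). With no treatment effect at those risks, a 10-point imbalance moves the risk difference by 0.10 × (49.6 − 16.4) = 3.3 points or 0.10 × (59.2 − 6.8) = 5.2 points. The planned difference is 23 points.

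**3. Power at the design rates.** Simulated logistic regression with likelihood-ratio tests, 80 vs 40, marginal risks held at 10% and 33%, 6,000 runs per row, no twins. In the triggered column the adjusted result replaces the unadjusted one when the baseline difference is significant at 5%. This treats the triggered result as decisive, which the plan does not.

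| Share | Odds ratio | Unadjusted | Prespecified | Triggered |
|---|---|---|---|---|
| 30% | 5 | 85.2% | 88.6% | 85.4% |
| 30% | 10 | 85.9% | 91.5% | 86.5% |
| 30% | 20 | 85.1% | 94.3% | 86.3% |
| 50% | 5 | 85.3% | 87.9% | 85.6% |
| 50% | 10 | 86.3% | 90.1% | 86.9% |
| 50% | 20 | 86.3% | 92.5% | 87.1% |
| 67% | 5 | 85.7% | 87.5% | 86.1% |
| 67% | 10 | 84.9% | 88.0% | 85.5% |
| 67% | 20 | 85.5% | 88.8% | 85.8% |

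Prespecified adjustment gains 1.7 to 9.2 points and the triggered rule 0.2 to 1.1. At an odds ratio of 1, all three stay between 85% and 86%. With a 20% risk in both groups (4,000 runs per row), type I error is about 4.5% to 6.2% across the three approaches.

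**4. Can an interaction be fitted?** With q = 0.5 there are about 20 non-sensitised placebo and 40 non-sensitised active infants. The chance that at least one of these cells has no event is 1 − (1 − (1 − p₀)²⁰)(1 − (1 − p₁)⁴⁰), where p₀ and p₁ are the placebo and active risks in non-sensitised infants.

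- Odds ratio 5 (p₀ = 16.4%, p₁ = 3.7%): 1 − 0.972 × 0.782 = 24%
- Odds ratio 20 (p₀ = 6.8%, p₁ = 1.15%): 1 − 0.754 × 0.370 = 72%

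Ordinary logistic regression would often fail to estimate the interaction.

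**The case against.** An unadjusted primary model is a legitimate prespecified choice. It matches the chi-squared sizing, its type I error is intact, and its confidence interval already reflects chance imbalance. The triggered re-run is explorative and cannot displace it. All of this stands, and it limits the point to efficiency and to the quality of the supporting analysis.

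Several stronger readings are tempting, and the article does not support them:

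- **The confirmatory result depends on choices made after seeing the data.** It does not; only the explorative re-run does.
- **The trial is underpowered.** The stated power reproduces. Larger gains from adjustment can be produced by assuming an active risk above 10%, but that is not the plan's assumption.
- **Baseline sensitisation is already available.** Blood is drawn at V1, but no V1 specific IgE assay is stated. With the visit table not shown, neither its presence nor its absence can be established.
- **Only infants sensitised at entry can have the event.** The endpoint is tied to sensitisation around the time of diagnosis. The half of infants in the Background is the share who become sensitised, not the share at V1. That entry sensitisation predicts strongly is plausible but unquantified here.
- **The trial cannot answer its own question.** The stated objectives concern infants with eczema as a whole, and an unscreened cohort does bear on safety without screening. What is missing is a stated analysis by entry sensitisation.

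The event count also limits the remedy: about 21 events do not comfortably carry treatment plus three covariates.

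**Conclusion.** The concern holds as a moderate weakness of the analysis plan, not as an error. The treatment-only model leaves precision unused, and the imbalance trigger selects covariates on the wrong criterion while recovering almost none of that precision. At the design rates, one prespecified covariate is worth about 2 to 9 points of power if its odds ratio is 5 to 20 and its share at entry is 30% to 67%. It costs essentially nothing if it is not prognostic. Those ranges are assumptions. The primary test, its error rate and the stated power are not in question.

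**What to change.** Before analysis:

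1. Name one, or at most two, prognostic baseline covariates in the primary model. First choice is V1 sensitisation (specific IgE > 0.1 kU/l to any of the four foods), if it was measured or can be measured from the V1 blood. Otherwise, or in addition, use V1 SCORAD, which the article says is collected.
2. Keep the unadjusted model as a sensitivity analysis and delete the imbalance-triggered re-run.
3. Report a marginal risk difference beside the odds ratio, because the adjusted odds ratio is conditional and differs from the unadjusted one.
4. Tabulate the primary endpoint and immediate reactions by V1 sensitisation, descriptively. Test the interaction only if event counts allow, for instance with a penalised fit.

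The cost is wording, possibly an assay of V1 serum, and a rule for infants without a V1 value that is squared with the plan's general strategy of not imputing. Because infants are unblinded one by one at their individual end of study and randomisation began in February 2020, the sponsor should also document that the change was made before the outcome data were analysed.

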### Participants

Infants with eczema 4–8 months of age are eligible for the trial. Eczema is defined as doctor´s diagnosed or parent-reported doctor´s diagnosed and will be finally evaluated by the study physician according to the criteria of Hanifin and Rajka [16]. Infants are excluded from the study if they have previously consumed HE, PN, or HN. Previous consumption of CM is no exclusion criterion, since infant formula commonly is based on CM and formula fed infants should be also addressed. Further exclusion criteria are wheat allergy (study product contains wheat), health issue (cardiac or congenital), and participation in another interventional trial.

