**Placebo group**				
**V1–V5/V6**	0	0	0	0

The sugar-free, rusk-like biscuit powder (3 g of powder/day using a measuring spoon) will be mixed with water, and optionally fruits, to a mash. The study product should be eaten on a daily basis throughout the study duration. The first feeding of the study product as well as every dose increase, each after 6 weeks, will be performed under medical supervision at the study center. In case of adverse events, the intervention may be individually modified according to investigator’s discretion.

In the placebo group, subjects consume daily a sugar-free rusk-like biscuit powder, without HE, CM, PN, and HN, analogously to the intervention group. The first and next dosing step feedings of the placebo study product will also be performed under medical supervision at the study site to maintain the blinding.

The first weaning food (e.g., vegetables) should have been successfully introduced for at least 1 week before feeding of the active/placebo product. Mothers will be encouraged to continue with breastfeeding while introducing weaning foods. Parents of both groups will be advised to avoid HE, PN, and HN or their products in their child’s diet. If the subject is unable to consume the recommended amount of rusk like biscuit powder, i.e., in the frame of feeding difficulties when weaning foods are introduced, the investigator and study physician may adjust the amount or dosing regimen within the patient’s diet. Non-compliance is defined as a repeated event of insufficient consumption of the intervention product, i.e., less than 3 times/week for 3 weeks (either during 3 consecutive weeks or three repeated events of 1 week). All participants may continue their usual medications, also those taken for any concomitant diseases, including wheezing and eczema, throughout the study. All subjects who will undergo an OFC at visit 6 will be advised to discontinue oral antihistamines 3–5 days before this procedure.

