### Primary endpoint

The primary endpoint is the occurrence of IgE-mediated food allergy determined with level 1 or 2 to at least one of the four foods (HE, CM, PN or HN) after 6–8 months of intervention (at around 1 year of age).

The diagnosis of food allergy will be determined according to the following levels:
Level 1: A positive oral food challenge at around one year of age in a child with allergen-specific IgE > 0.1 kU/l or skin prick test (SPT) wheel size > 3 mm.Level 2: A systemic reaction with objective symptoms upon accidental exposure in a child with specific IgE to one of the four intervention foods > 0.1 kU/l or SPT wheel size > 3 mm.Level 3: Allergen- or allergen component-specific IgE above the 90% predicted probability for this individual food [18, 19].

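### Cow's milk (CM) subpopulations are to be analysed separately, without the interaction term the other subgroups get, and the wording does not tie CM status to baseline

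*Protocol article*

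**What the plan says.** All of this is in the Methods of the protocol article.

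- **Primary endpoint.** IgE-mediated allergy at level 1 or 2 "to at least one of the four foods (HE, CM, PN or HN"), so a CM allergy alone counts as an event.
- **Participants.** "Previous consumption of CM is no exclusion criterion, since infant formula commonly is based on CM and formula fed infants should be also addressed".
- **Intervention.** "Parents of both groups will be advised to avoid HE, PN, and HN or their products". CM is not on that list. Table 1 gives the active product 2.0 to 167 mg of CM protein daily, and the placebo product none.
- **Statistical analysis, listed subgroups.** "Subgroup analysis will be performed by additionally including the subgroup variable and the interaction term (subgroup*treatment group) into the primary analysis model". The list includes breastfed versus formula-fed children but not CM consumption.
- **Statistical analysis, CM.** "In case subpopulations regarding to the consumption of CM exist, these subpopulations will be analyzed separately (FAS population"). What defines the subpopulations, and at which visit, is not stated.
- **Study procedures.** At V1, "relevant medical history, medication, and nutrition will be recorded". Nutrition is recorded again at V2, V3, V4 and V5.
- **Status.** Apart from the primary analysis, "All other analysis will be considered explorative".

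**The concern.** CM exposure is a foreseeable effect modifier. For HE, PN and HN the arms differ by exposure against advised avoidance. For CM they differ by study-product CM on top of an unrestricted background diet against that same diet. The contrast is therefore reduced for infants who already consume CM, and a reader will want to know whether the treatment effect differs by CM status.

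The planned analysis does not answer that, for two reasons.

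1. Two separate analyses give two p-values but no test of their difference. A significant result in one subset beside a non-significant one in the other invites the conclusion that CM status matters, even when the effects are equal.
2. With no time point fixed, subsets could be formed on CM consumption during follow-up. That consumption may be affected by treatment or by a CM reaction, and CM reactions are part of the outcome. Such subsets would lose the protection of randomisation.

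**Working it through.** **1. The plan's own figure.** Inputs from Sample size calculation: 80 active and 40 placebo analysed, 10% vs 33%, two-sided chi-squared test at 5%. Summing the binomial probabilities of all outcome tables in which the Pearson test rejects gives a power of 0.862. The stated figure of at least 80% reproduces.

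**2. Separate analyses under one common effect.** Assume CM consumers and non-consumers each make up half the sample (40/20 in each) and the effect is 10% vs 33% in both. The split is an assumption, as the article gives no share of CM consumers.

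- Power in each half, by the same exact method: p = 0.574.
- Exactly one half significant: 2 × p × (1 − p) = 2 × 0.574 × 0.426 = 0.489.
- Both significant: 0.574² = 0.329. Neither: 0.426² = 0.181.

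With an assumed 25%/75% split (20/10 and 60/30), the powers are 0.331 and 0.768. Exactly one is then significant with probability 0.331 × 0.232 + 0.768 × 0.669 = 0.591.

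So with no true difference in effect, the pattern that looks like a difference appears about half the time or more. An interaction test at the 5% level is built to flag a difference in about 5% of such cases.

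**3. Baseline versus later CM status.** This illustration assumes no treatment effect at all. Assume 33% of infants are high risk with a 70% allergy rate. For an overall rate of 33%, the low-risk rate is (0.33 − 0.33 × 0.70) / 0.67 = 14.8%. Let 80% consume CM among low-risk infants in both arms and among high-risk placebo infants, and vary the share among high-risk active infants.

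| High-risk active infants consuming CM | Odds ratio, consumers | Odds ratio, non-consumers |
|---|---|---|
| 80% (status independent of arm, as at baseline) | 1.00 | 1.00 |
| 60% | 0.86 | 1.48 |
| 40% | 0.70 | 1.85 |

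For the 60% row, the rate among active consumers is (0.33 × 0.6 × 0.70 + 0.67 × 0.8 × 0.148) / (0.33 × 0.6 + 0.67 × 0.8) = 0.297, against 0.33 on placebo. The odds ratio is (0.297/0.703) / (0.33/0.67) = 0.86. All inputs except the overall 33% are assumptions; the table shows the direction of the risk, not its size in this trial.

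**4. Dilution of the primary endpoint.** Let c be the placebo risk of CM-only allergy (not given, so assumed), and let all other allergy fall by the planned ratio 10/33. If treatment has no effect on CM-only allergy, the active risk is (0.33 − c) × 10/33 + c. If it has half the planned relative reduction on CM-only allergy, the last term becomes c × [1 − 0.5 × (1 − 10/33)]. Exact power at 80/40:

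| c | Four foods, no CM effect | Four foods, half CM effect | Three foods (HE, PN, HN) |
|---|---|---|---|
| 2 points | 80% | 83% | 84% |
| 4 points | 74% | 80% | 81% |
| 6 points | 67% | 77% | 77% |

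The loss depends on both assumptions. With half the planned effect on CM-only allergy, the three-food endpoint has practically no advantage.

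**The case against.** The strongest reply is that this is one explorative analysis in a condensed article. It cannot alter the single confirmatory test, and the full protocol or SAP may fix CM status at V1. Participants speaks of CM consumption before entry, so a baseline reading of the CM sentence is natural. The breastfed versus formula-fed subgroup already has an interaction term and, since that section links prior CM to formula, partly covers baseline CM exposure. Most of this stands and limits the severity. It does not remove the point: analysing separately is a stated choice that departs from the rule for the listed subgroups in the same paragraph, and feeding mode is not CM consumption, because complementary foods may also contain CM.

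Two stronger readings are tempting, and the article supports neither.

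- *A reader might infer that CM-only allergies are events the design cannot influence, so the primary endpoint is diluted.* The active arm receives CM daily from the product, while a placebo infant with no CM in the background diet receives none. The contrast is reduced, not absent. Any power loss rests on an assumed CM-only rate and an assumed CM effect, and dilution does not raise the type I error.
- *A reader might infer that the trial will select on CM consumption after randomisation.* The wording permits it but does not say so.

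**Conclusion.** The point holds as a minor one about the method of an explorative subgroup analysis. CM status is the subgroup variable with a clear reason in the design, yet the stated analysis gives it no test of effect difference and does not anchor it at baseline. Under an identical effect of 10% vs 33% in both subsets, exactly one is significant in about 49% of trials with an assumed equal split and about 59% with an assumed 25%/75% split. The bias from subsets formed after randomisation is possible under the wording; its size cannot be known from the article. The primary analysis, its type I error and the stated power are not called into question.

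**What to change.** In Statistical analysis, replace the CM sentence with wording to this effect: CM consumption (yes/no), defined from the nutrition record at V1, is added to the list of subgroups and analysed in the FAS by including CM consumption and its interaction with treatment group in the primary model; subgroup odds ratios with confidence intervals are reported from that model; no subset is formed on CM consumption after V1.

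Nothing is lost. With two binary factors and their interaction, the model gives the same subgroup odds ratios as separate fits, apart from the handling of twin correlation, and adds the missing test. That test will have low power at this sample size, so the estimates and intervals matter more than its p-value.

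The existing secondary endpoint on HE, PN and HN can be reported beside the primary result as supportive. Ranking it first would have no inferential effect among explorative secondaries.

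The cost is wording only, as the V1 nutrition data are already collected. The change recovers no power for the four-food primary endpoint and is not meant to.
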